## Abstract

**Background:**

Males in Australia and many other countries account for three-quarters of all deaths by suicide. School-based programs to support young men’s wellbeing have become increasingly common in recent years and show much promise to tackle the issue of male suicide by fostering protective factors and mitigating harmful factors. However, only a few of these programs have been evaluated. This trial seeks to address the lack of knowledge about the potential for school-based gender-transformative programs to have a positive impact on boys. *Breaking the Man Code* workshops, delivered by *Tomorrow Man* in Australia, challenge and transform harmful masculinities with young men with a view to ultimately reducing their suicide risk. The trial aims to examine whether adolescent boys who participate in the *Breaking the Man Code* workshop demonstrate an increase in their likelihood of seeking help for personal or emotional problems compared to boys waiting to take part in the workshop.

**Methods:**

A stratified cluster randomized controlled superiority trial with two parallel groups will be conducted. Schools will be randomly allocated 1:1, stratified by location of the schools (rural or urban), state (Victoria, NSW, or WA), and mode of workshop delivery (face-to-face or online), to the intervention group and waitlist control group.

**Discussion:**

The *Breaking the Man Code* workshops show great promise as a school-based prevention intervention. The trial will fill a gap in knowledge that is critically needed to inform future interventions with boys and men. Some methodological challenges have been identified related to the COVID-19 pandemic in Australia, such as delays in ethics approvals and the need for *Tomorrow Man* to introduce an online delivery option for the workshop. The trial protocol has been designed to mitigate these challenges. The findings from the trial will be used to improve the workshops and will assist others who are designing and implementing suicide prevention interventions for boys and men.

**Trial registration:**

Australian New Zealand Clinical Trials Registry (ACTRN12620001134910). Registered on 30 October 2020

## Administrative information

Note: the numbers in curly brackets in this protocol refer to SPIRIT checklist item numbers. The order of the items has been modified to group similar items (see http://www.equator-network.org/reporting-guidelines/spirit-2013-statement-defining-standard-protocol-items-for-clinical-trials/).

## Introduction

### Background and rationale {6a}

Males in Australia and many other countries account for three-quarters of all deaths by suicide [1, 2]. In Australia, the rates of suicide among males are higher than those of females across all age groups [1]. Among young Australians, rates of suicide and suicide-related behavior remain high despite a national priority for the prevention of youth suicide. The suicide of a young person has a devastating ripple effect on friends, family, and the community [3].

The higher rate of suicide among males has been attributed to several factors including lethality of means, substance use and associated impulsivity, reduced social connectedness, reduced help-seeking, and—perhaps underpinning these factors—conformity to some masculine norms [4–7].

While some masculine norms have positive impacts on wellbeing [8], conformity to masculine norms such as self-reliance has been linked to increased suicidal ideation and behavior [9, 10]. This may be because some masculine norms act to discourage seeking help for emotional problems, which is perceived as weakness or failure [11–13]. These masculine norms are laid down early in life with men reporting conformity to these norms from adolescence [14, 15]. Given the gendered nature of suicide and the role of masculine norms, a gendered focus that attends to the social context of suicide experienced by men has long been recommended for suicide prevention interventions [16, 17]. The fact that gender role socialization starts early in life suggests the need for early interventions with adolescent males to ameliorate negative impacts of rigid adherence to masculine norms. Reduction in self-reliance in particular, and increases in help-seeking, may ultimately reduce the rate of suicide among men.

Despite the strong case for gendered programs and the importance of the social context for male suicide risk, there is a limited knowledge base regarding the use of such programs [18]. Few suicide prevention interventions have specifically targeted males, and fewer still have focused on the role of masculine norms as a determinant of suicide. A scoping review of men’s suicide prevention published in 2017 identified only six interventions targeting men [19].

School-based programs designed to specifically support young men’s wellbeing have become increasingly common in recent years. In Australia, *Tomorrow Man*’s *Breaking the Man Code* workshops (tomorrowman.com.au), the *Man Cave* program (themancave.life), and Menslink’s *Silence is Deadly* program (menslink.org.au/silence-is-deadly) are three examples. They each adopt an upstream approach to male suicide prevention by focusing on reducing conformity to harmful masculine norms and increasing help-seeking. However, the evidence base for the effectiveness of gendered school-based programs to bring about these and other positive impacts for young men is lacking. A systematic review of young men’s wellbeing programs by Gwyther and colleagues, published in 2019, found 40 studies [20]. Of which, only four of these addressed harmful aspects of masculinity to bring about positive changes for young men (labeled “gender transformative”), and a further 10 tailored content to young men, but did not explicitly address conformity to harmful masculine norms (“gender sensitive”). Each of these interventions reported some positive impacts but no changes in any variables related to masculinity. The review concluded with overall support for the effectiveness of programs for boys and young men, particularly via gendered interventions and school-based environments. However, it cautioned that many programs remain unevaluated and that there is a need to determine which approaches work best. Another recent review by Calear and colleagues explored psychosocial interventions for youth suicide [21]. This review identified 28 trials and found that just over half of the programs had an impact on reducing suicidal ideation, suicide attempts, or self-harm. However, none of the trials focused exclusively on young males or attended to masculine norms. The authors concluded that further research is needed to strengthen the evidence base for youth suicide prevention interventions. Like Gwyther and colleagues, Calear and colleagues highlighted the potential for school-based programs. Recently, Calear and colleagues have published the findings of their trial of the *Silence is Deadly* program, an upstream public health intervention for increasing help-seeking intentions for mental disorders and suicide for adolescent males. This gender transformative program was found to significantly increase help-seeking intentions from friends [22].

In summary, school-based gender-transformative programs are showing some promise as an upstream approach to male suicide prevention; however, more research is needed to confirm impacts for participants and understand more about the process by which impacts are achieved.

This trial seeks to address current knowledge gaps in the potential for school-based gender-transformative programs to have a positive impact on the help-seeking intentions of adolescent boys. Between 2017 and 2021, *Tomorrow Man* has delivered over 750 *Breaking the Man Code* workshops that challenge and transform harmful masculinities with Australian adolescent males with a view to ultimately reducing their suicide risk around Australia. However, these workshops have not been formally evaluated in terms of their impact on participants. Findings about the impact of the workshops will provide lessons for suicide prevention programs that focus on transforming potentially harmful masculine norms to bring about positive mental health outcomes for young males.

This trial aims to determine the impact of *Breaking the Man Code* workshops on adolescent boys.

### Objectives {7}

The objective of the trial is to determine the impact of the *Breaking the Man Code* workshops on adolescent boys’ (in year 10, 11, or 12) intentions to seek help for a personal emotional problem, conformity to masculine norms, depression risk, perceived social support, and quality of life.

### Trial design {8}

This study is a stratified cluster randomized controlled trial with two parallel groups. Schools will be randomized to the intervention group and waitlist control group with a 1:1 allocation stratified by location of the schools (rural or urban), state (Victoria, NSW, or WA), and mode of workshop delivery (face-to-face or online),

## Methods: participants, interventions, and outcomes

The trial methods are reported using the SPIRIT reporting guidelines as shown in the checklist [23].

### Study setting {9}

The trial will be conducted within secondary schools in Australia in New South Wales, Victoria, and Western Australia. Recruitment of schools began in late 2020. These three states were chosen as they are the states of Australia where Tomorrow Man undertakes most of their work. There will be a mix of rural, urban, private, and public schools. All schools in these three states who receive a *Breaking the Man Code* workshop within the trial period are eligible to take part (subject to relevant ethics approvals) and will be invited to participate. Recruitment of students into the study began in the second school term of 2021 (April). Data collection will occur in the 2021 and 2022 school years.

### Eligibility criteria {10}

Eligible participants will be male senior secondary school students in year 10, 11, or 12 who are enrolled to take part in a *Breaking the Man Code* workshop in 2021 or 2022 within their school and have parental/guardian informed consent.

School inclusion:
Request a *Breaking the Man Code* workshop for their year 10, 11, or 12 males in 2021 or 2022.Agree to schedule the workshop within either the intervention period or the waitlist period (after the trial is complete) as instructed by the researchers.Agree to distribute study information to parents of boys enrolled in the workshop and to allocate two class times, 6–8 weeks apart, for students to complete the baseline and follow-up questionnaire.

Student inclusion:
Student within a participating school in years 10, 11, or 12Self-identified maleEnrolled to take part in a *Breaking the Man Code* workshopParent has provided consent for them to take part in the trial

There are no exclusion criteria.

### Who will take informed consent? {26a}

The principals of participating schools will provide consent for school participation. Parental (or guardian) consent will be sought in all schools. The method of parental consent will be determined in collaboration with each school. To maximize response, the method will ideally be the same method of consent that each school uses for their other student activities (such as excursions and incursions). This will likely involve using school digital platforms (such as Daymap.net) or sending emails to parents with links to online consent procedures. Hard copies of study information and consent forms can be sent home with students, for return to the researchers in a provided prepaid envelope, for those without online access. Parents or guardians will be asked to provide their son’s school name and school email address which will be used by an independent data management company (Logicly) to provide students with the Plain Language Statement, consent form, and a link to the online survey once parental consent is received. Students whose parents have consented to their participation will be asked for their informed assent online within the allocated class time at school after reading the Plain Language Statement.

### Additional consent provisions for collection and use of participant data and biological specimens {26b}

Not applicable, no biological specimens collected.

## Interventions

### Explanation for the choice of comparators {6b}

The trial will compare participants who receive the *Breaking the Man Code* workshop within their school with those who are waitlisted to receive the workshop and receive only their usual school curriculum. These conditions were chosen so that no school would be denied the opportunity to receive the intervention, as both groups will have shown an interest in receiving the workshops. It is expected that the two groups of schools (intervention and waitlist) will be similar given that they are taken from the same population (schools requesting a workshop).

### Intervention description {11a}

The intervention group will receive the *Breaking the Man Code* workshop. This workshop will be delivered in class time at school by a *Tomorrow Man* trained facilitator. The workshops are delivered over 2 h in a face-to-face or an online format (i.e., via a video meeting platform) to groups of 30–35 male students. Prior to the COVID-19 pandemic, workshops were delivered face-to-face only. In response to the pandemic, and associated lockdowns and travel restrictions, the online mode was developed in 2020 during the design phase of the trial. The workshop content is similar in both delivery modes, with small adjustments. The mode of delivering is now generally chosen based on school preference, facilitator availability (particularly when the facilitator is required to travel to rural areas), and, where relevant, COVID restrictions. One facilitator usually provides all the workshops within one school, with up to six facilitators delivering the workshops across schools nationally. The average number of workshops per school is three, with an average of 33 students per workshop.

The interactive *Breaking the Man Code* workshops facilitate honest and authentic conversations with year 10, 11, and 12 male students, in order to define a masculinity that “generates purpose, pride, and health for the men of today and tomorrow.” The workshops aim to develop protective factors such as positive attitudes towards help-seeking, emotional expressiveness, and social support. The workshop involves discussion about the stereotypes of what it means to be a man in Australia today, and the impacts that these can have on men’s mental health. It explores the (unwritten) rules that exist for men on how to behave (the “man code”) and investigates why men and boys feel obliged to live up to these expectations and stereotypes. The workshop then unpacks the impact of the “man code” on boys and men and allows boys to share their experience living with the stereotypes while encouraging them to question norms and redefine their own rules.

### Criteria for discontinuing or modifying allocated interventions {11b}

There will be no modification to the interventions. Schools and participating students will be free to withdraw from the trial at any point. This will not impact on their involvement in the workshop. Students who choose not to take part in, or complete, the trial will still be able to take part in the workshop. Facilitators will monitor students for signs of distress during the workshop and the decision to withdraw students from the workshop will be made collaboratively between the facilitators and the schools. The researchers will not be involved in this process.

### Strategies to improve adherence to interventions {11c}

All students who complete the baseline questionnaire will be invited to complete the follow-up questionnaire, regardless of whether or not they attend the workshop (e.g., due to illness). Logicly (the independent data manager sub-contractor) will monitor parental consent, student assent, and student survey completion rates per school while maintaining allocation blinding and will report this to the researchers weekly. An Advisory Group, comprising experts in men’s and youth mental health, and a Consumer Reference Panel, comprising young males who have previously received the workshop, are supporting the trial. These groups will provide advice regarding strategies to improve participant adherence.

### Relevant concomitant care permitted or prohibited during the trial {11d}

There are no restrictions on concomitant care.

### Provisions for post-trial care {30}

Any participants who suffer harm, such as psychological distress, from the trial will be supported by their school’s welfare processes.

### Outcomes {12}

#### Primary outcome

Difference between the intervention and waitlist control groups at follow-up in the mean change in intentions to seek help as measured by an adapted version of the General Help Seeking Questionnaire (GHSQ) [24] at 8 weeks post-baseline.

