#### Secondary outcomes

Difference between the two study groups at 8 weeks post-baseline in:
Mean change in conformity to masculine norms as measured by the Conformity to Masculine Norms Inventory (CMNI-22) [25].Mean change in depression risk as measured by the Male Depression Risk Scale Short Form [26].Mean change in perceived social support as measured by the Modified Medical Outcomes Study Social Support Survey (MOS-SS) Emotional/Informational support subscale [27]Mean change in quality of life as measured by the Child Health Utility Instrument (CHU-9D) [28]

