For schools in the intervention group, soon after randomization, schools will schedule a class time for all the male students who are enrolled to take part in the workshop. This class time will be within the 2 weeks prior to the workshop. The school will advise the researchers of this class time and the researchers will direct Logicly to send a second email to students with parental consent. The email will contain a link to the Plain Language Statement, assent form, and baseline questionnaire. The school staff member will activate the baseline questionnaire within the class time using a link provided to them by Logicly. After reading the Plain Language Statement and providing their assent, the students will have access to complete the online survey which will take about 20 min. Intervention group schools will then receive the workshop within the following 2 weeks. Schools will be asked to schedule a second-class time with students 4 to 6 weeks after students received the workshop to administer the follow-up questionnaire. Prior to this class, students who completed the baseline questionnaire will receive an email containing a link to the deactivated online follow-up questionnaire. Within the class time, a staff member will direct students to the email, if they have received it. The staff member will activate the follow-up questionnaire and the students will complete it

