For schools in the waitlist group, soon after randomization, the schools will schedule a class time for all the male students who are enrolled to take part in the workshop. The school will advise the researchers of this class time and the researchers will direct Logicly to send an email to students with parental consent containing a link to the Plain Language Statement, assent form, and baseline questionnaire. The school staff member will activate the baseline questionnaire within the class time using a link provided to them by Logicly. After reading the Plain Language Statement and providing their assent, the students will have access to complete the online survey which will take about 20 min. The schools will then provide school as usual for the students over the following weeks. Schools will be asked to schedule a second class time for students to complete the follow-up questionnaire 6 to 8 weeks after the baseline questionnaire. The staff member will activate the questionnaire and the students will complete it. They will receive the workshop after the second survey has been completed by the students.

In either group, if a student has completed the baseline questionnaire, but cannot locate the email for the follow-up questionnaire, then an automated process will enable the teacher to provide the student email to Logicly who will resend the email.

If schools or individual participants withdraw from the trial at any time (prior to baseline or follow-up questionnaire assessment), the data provided by participants up to that point will be included in the trial.

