## Data collection and management

### Plans for assessment and collection of outcomes {18a}

Outcome measures will be collected from students at baseline after randomization of schools. For the intervention group, data will be collected at baseline within 2 weeks of the intervention being delivered. The follow-up questionnaire will be administered 4–6 weeks after the workshop. For the waitlist control group, baseline and follow-up data collection will occur 6–8 weeks apart before the workshop is delivered.

For both groups, the baseline and follow-up questionnaires will be administered online within an allocated class time. The baseline questionnaire will include demographic questions and the measures related to the primary, secondary, and economic outcomes that are described below. The follow-up questionnaire will be a repeat of the baseline questionnaire, minus the demographic questions, with the addition of some open-ended questions for the intervention group.

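### Outcomes are defined at week 8, the far edge of the follow-up windows, and the intervention-arm instructions omit the 6–8 week spacing, so intervention schools can be measured earlier than any waitlist school

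*Protocol article*

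**What the plan says.** The protocol article gives follow-up timing in four places.

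- **Outcomes {12}.** The primary outcome is the change in the "General Help Seeking Questionnaire (GHSQ) [24] at 8 weeks post-baseline". The secondary outcomes are headed "Difference between the two study groups at 8 weeks post-baseline in". Neither has a window.
- **Participant timeline {13}, intervention schools.** On the baseline questionnaire: "This class time will be within the 2 weeks prior to the workshop". Follow-up is "4 to 6 weeks after students received the workshop". Plans for assessment and collection of outcomes {18a} repeats both rules: "data will be collected at baseline within 2 weeks of the intervention being delivered" and "The follow-up questionnaire will be administered 4–6 weeks after the workshop".
- **Participant timeline {13}, waitlist schools.** They are to "complete the follow-up questionnaire 6 to 8 weeks after the baseline questionnaire". Section {18a} gives the same spacing.
- **Eligibility criteria {10}.** Every school, whichever arm it later joins, agrees to "allocate two class times, 6–8 weeks apart, for students to complete the baseline and follow-up questionnaire".

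The primary model in Statistical methods {20a} has terms for study group, baseline score, the stratification factors and school. It has no term for time elapsed since baseline.

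**The concern.** The two arms count follow-up from different events: the workshop in one, the baseline questionnaire in the other. The spacing rule that would bring them together stands only among the school inclusion criteria. It is absent from both places that tell an intervention school when to hold its second class. A school working from those instructions could survey at week 4 or 5, when no waitlist school may be surveyed.

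Two things are at stake. The first is what the result describes. The estimate would be reported as an 8-week effect, although most follow-ups in either arm would be expected before week 8. The second is comparability. The primary contrast is a difference in change since baseline. If scores drift with time, from the school calendar or from repeated questioning, a systematic difference in interval puts part of that drift into the workshop effect. Schools book the follow-up class and know their allocation (Who will be blinded {17a}), so blinding does not protect the interval.

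**Working it through.** **Inputs from the article**
- Baseline to workshop, intervention: b = 0 to 2 weeks ({13}, {18a}).
- Workshop to follow-up, intervention: f = 4 to 6 weeks ({13}, {18a}).
- Baseline to follow-up, waitlist: 6 to 8 weeks ({13}, {18a}).
- Questionnaire spacing, all schools: 6 to 8 weeks ({10}).
- Target difference 3 points, SD 10, 90% power, two-sided 5% (Sample size {14}).

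**Assumptions, not in the article**
- Independent, uniform scheduling within each window.
- GHSQ drift of 0.1 to 0.3 points per week.

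**1. The stated time point.** The largest value of b + f is 2 + 6 = 8 weeks. An intervention school reaches week 8 only with baseline a full two weeks before the workshop and follow-up a full six weeks after it. With b = 1, the latest follow-up is 1 + 6 = 7 weeks. In the waitlist arm week 8 is also just the upper limit.

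**2. Windows from the arm-specific rules alone**
- Intervention: from 0 + 4 = 4 to 2 + 6 = 8 weeks.
- Waitlist: 6 to 8 weeks.

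The windows overlap from 6 to 8 weeks. Only the intervention arm can fall between 4 and 6.

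**3. Adding the spacing criterion.** It requires 6 ≤ b + f ≤ 8. Because f is at most 6, the permitted interval runs from 6 to 6 + b weeks. This is never empty: even with b = 0, follow-up at exactly 6 weeks meets every rule. The criterion and the workshop-anchored rule are therefore compatible, and together they keep both arms within 6–8 weeks.

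**4. Mean intervals under uniform scheduling**
- Waitlist: (6 + 8)/2 = 7.0 weeks.
- Intervention, criterion not applied: 1 + 5 = 6.0 weeks. The sum of the two uniforms is symmetric about 6, so 50% of follow-ups fall before week 6 (a simulation of one million draws gave 6.00 and 50.0%).
- Intervention, keeping only intervals of at least 6 weeks: the density falls linearly from week 6 to week 8, so the mean is 6 + 2/3 = 6.67 weeks.

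The gap to the waitlist arm is 1.0 week without the criterion and 0.33 week with it.

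**5. Size on the GHSQ scale**
- Without the criterion: 1.0 × (0.1 to 0.3) = 0.1 to 0.3 points, or 3–10% of the 3-point target.
- With it: 0.33 × (0.1 to 0.3) = 0.03 to 0.1 points, or 1–3% of the target.
- For scale, 90% power at 3 points implies a standard error of about 3/(1.96 + 1.28) = 3/3.24 = 0.93. The larger range is roughly 0.1 to 0.3 standard errors.

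**6. Sample size.** The calculation has no timing input. It reproduces: 234 per arm before clustering; a design effect of 1 + 19 × 0.03 = 1.57 with 25 × 0.8 = 20 completers per school; 2 × 234 × 1.57 ≈ 735 completers, or 36.7 schools; 38 for equal arms, plus 2 for loss, gives 40 schools and 1000 students. This point leaves it unchanged.

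**The case against.** The strongest reply is that the inclusion criterion already settles the matter. It binds every school, it can be met together with the intervention-arm rules for any permitted baseline date, and 2 weeks plus 4–6 weeks is exactly 6–8 weeks, which suggests the windows were built to fit. On that reading a week-4 follow-up is a breach of the plan, and only the week-8 label is loose. The drift rate also has no source in the article, and even the larger bias is a fraction of a standard error.

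Much of this stands. A reader might infer that the arms will be measured at different times. The documents do not support that: the windows overlap from 6 to 8 weeks, and the rules allow a difference without imposing one. A reader might also infer a material distortion of the QALYs. That would depend on summing utility over actual intervals, and the article states no such method, so no QALY figure is claimed.

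What the reply does not remove is the mismatch in the text. The criterion is missing from the two sections that schedule intervention schools, and the outcome definition names a single week that the schedule reaches only at its limit. Even with the criterion enforced, the six-week cap after the workshop pulls intervention follow-ups towards week 6, while waitlist schools have the whole window.

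**Conclusion.** The point holds as an inconsistency to reconcile. The outcome time point, the spacing promised by all schools and the arm-specific instructions do not say the same thing, and the instructions as written let intervention schools be measured up to two weeks before the earliest waitlist follow-up.

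The expected effect on the primary estimate is small: 0.03 to 0.1 GHSQ points if the spacing criterion is enforced, 0.1 to 0.3 if it is not. Both ranges rest on the assumed uniform scheduling and the assumed drift. The better reason to act is that the time point of the primary outcome should match what is measured, in the same window in both arms. The size of the bias does not make this a critical defect. It is worth correcting because the correction is cheap.

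**What to change.** 1. In Participant timeline {13} and Plans for assessment and collection of outcomes {18a}, count follow-up from the baseline questionnaire in both arms, with the 6–8 week window already in the eligibility criteria.
2. State how that window relates to the existing workshop-to-follow-up interval, including which takes precedence when a school cannot conveniently meet both.
3. In Outcomes {12}, replace the single week for primary and secondary outcomes with the same window.
4. Give intervention schools a matching instruction when they book the second class.
5. Optionally, add a sensitivity analysis that adjusts the primary model for days since baseline. Its detail belongs in the statistical analysis plan, to which section {20c} already refers sensitivity analyses.

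The cost is wording in three sections and one scheduling instruction. No visits are added and the sample size stays the same. The small downside is that, if the baseline-anchored window takes precedence, time from workshop to follow-up may exceed 6 weeks where baseline was held close to the workshop, up to 8 − 0 = 8 weeks at the extreme.
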